## Abstract

**Background:**

Youth of color who live in urban communities face disproportionate anxiety levels due to systemic inequities, including exposure to violence, economic instability, and neighborhood disadvantage. Despite increased need, these communities often lack accessible mental health interventions.

**Objective:**

This study presents a protocol for an anxiety prevention intervention developed through a community-based participatory approach that is tailored to urban youth of color using community-based participatory research methods.

**Methods:**

The intervention, co-developed with a community partner and guided by a youth advisory board, includes 5 structured weekly sessions on psychoeducation, coping skills, and role-playing exercises. Facilitators trained in social work or psychology will deliver the intervention, with at least 1 facilitator from the target community ensuring cultural relevance. Recruitment will occur through collaboration with a local high school, with counselors identifying high-risk youth. We will enroll a sample of 30 high school–aged youth at minimum (maximum 50 youth) into the study. Two cohorts of youth will participate in the study. The groups will be separated by sex (male and female). The primary outcome is reduction in anxiety, measured by the Generalized Anxiety Disorder-7 scale. Data will be collected at baseline, after the intervention, and during follow-up assessments (3 months after). Statistical analyses will include parametric tests (eg, repeated measures ANOVA and 1-tailed *t* tests) to compare anxiety reduction across groups.

**Results:**

This pilot intervention is a part of a larger study that began in September 2020 and ended in August 2025. Enrollment for the pilot intervention began in May 2025. The anxiety intervention is expected to reduce anxiety among a high-risk group of youth. Methods to improve facilitator fidelity to the intervention model are expected to support high fidelity to the curriculum.

**Conclusions:**

This study highlights the development of a new anxiety intervention using a community-based participatory approach. Findings will be reported and used to scale up the pilot intervention into a larger clinical trial to serve a larger population of youth in the targeted community. In addition, the results will contribute to knowledge on improving mental health accessibility for marginalized youth. If effective, this model could be expanded to support youth in other underresourced communities.

## Introduction

### Background

In the United States, the prevalence of anxiety among youth has continued to steadily rise over the past few years [1]. Findings from the National Survey of Children’s Health showed a 27% increase in anxiety from 2016 to 2019 and, by 2020, 5.6 million children had been diagnosed with anxiety problems [1]. Increased anxiety among youth of color has also been observed over the past few years [2,3]. Addition, the rate of increase in anxiety disorders among Black people overall exceeded the rate seen for White people over the same period (17.1% for Black people vs 4.5% for White people) [2]. Moreover, data from the National Comorbidity Survey, which assessed for lifetime prevalence of mood and anxiety disorders among English-speaking households, revealed that Hispanic or Latinx youth were at the highest risk for mood and anxiety disorders compared to non-Hispanic White adolescents [3]. Besides disparities across racial and ethnic groups, adolescents from low-income households, especially those in urban communities, are at higher risk for anxiety compared to their peers from high-income households [4,5].

While there may be many factors that play a role in the development of anxiety symptoms among youth, research has shown that increased rates of mental health issues, specifically among urban youth, are significantly related to the environment in which they live and if they are at a neighborhood disadvantage [6]. Characteristics of the urban environment, such as community violence, gang activity, substance use, and poverty, disproportionately affect urban youth and increase their exposure to potentially traumatic events such as incidents related to community-level violence [7]. This type of trauma exposure has been linked to the development of depression, anxiety, and early-age substance use. Similarly, neighborhood disadvantage consisting of limited resources, lack of safety, subpar housing, and unemployment has also been associated with anxiety among urban youth [5,7]. As evidenced, due to the amount of stressors youth are exposed to in urban communities, anxiety among this population is a significant public health problem, and the lack of resources in these communities exacerbates these issues. Underresourced urban communities are in dire need of services and programs that can improve the climates of spaces youth spend the majority of their time in, which can improve the overall mental health of the youth living in these communities.

As youth spend approximately one-third of their early developmental years within an academic setting, schools have been identified as effective sites for the implementation of mental health programming [8,9]. Due to schools being such key places for youth, school-based interventions have the opportunity of reaching youth who may have been previously unidentified or untreated [10]. Compared to community-based mental health clinics and primary care settings, delivering interventions in urban school settings, as an example, can address some of the many barriers faced by urban youth in underresourced communities such as removing the need for travel, unfamiliarity, cost, and time [11].

### Importance of Community-Based Participatory Research

Community-based participatory research (CBPR) can be used as a critical approach in the development and implementation of mental health interventions, particularly in urban communities, as it is essential that these programs and interventions incorporate the voices of those living in these communities [12]. Researchers agree that the insights gained from receiving direct feedback from community members enhance the researchers’ understanding of the problems affecting the community while also building on the strengths of the community. CBPR engages community members as equal partners and cogenerators of knowledge throughout the research process, ensuring that interventions are culturally relevant, contextually appropriate, and responsive to the specific needs of the population [12]. This collaborative methodology has proven effective in addressing systemic issues that contribute to mental health disparities, such as poverty, exposure to violence, and inadequate access to health care services [13]. Furthermore, CBPR fosters trust between academic researchers and historically marginalized communities, promoting the sustainability of mental health programs and enhancing their real-world impact [14].

Youth advisory boards (YABs) within CBPR projects, composed of young individuals from the very communities being studied, with diverse perspectives, play a pivotal role in ensuring that interventions are youth centered, engaging, and accessible. In recent years, research has shown the importance of including youth feedback in the development of mental health interventions for them [15]. It has been shown that the use of YABs helps to ensure that youth voices are heard within systems and helps to identify youth priorities related to mental health needs and issues [16]. Research also demonstrates that the use of youth participatory methods is helpful in obtaining meaningful insight from youth, engages them in the research process, and therefore empowers youth to be coparticipators in problem solving [17]. On a larger scale, including youth participation in research can also lead to more effective community-level policies that directly improve health outcomes and quality of life of this population [18]. By having youth actively participating in the co-design process, YAB members provide valuable insights into the language, delivery methods, and intervention components that resonate with their peers. Their involvement fosters a sense of ownership and empowerment, increasing the likelihood of program uptake and success.

Pertaining to youth mental health outcomes, engaging community members and YABs is crucial in developing effective interventions for young people, particularly in addressing mental health challenges such as anxiety. Community members offer invaluable insights into local needs, cultural dynamics, and systemic barriers that can influence the implementation and sustainability of interventions [18]. Their lived experiences help shape programs that are contextually relevant and responsive to the specific challenges faced by youth in their communities.

### Purpose of This Study

The purpose of this protocol is to outline steps that were taken for the development of a pilot feasibility trial of a community-based psychoeducational intervention for anxiety designed to alleviate anxiety symptoms among youth living in an urban environment. This curriculum was developed through a collaborative partnership with a licensed clinical social worker who was born and raised in the study setting, ensuring that the intervention is both culturally relevant and grounded in the lived experiences of the community. Recognizing the unique stressors faced by youth in urban settings, including exposure to community violence, economic instability, and limited access to mental health resources, this program integrates evidence-based anxiety prevention strategies with community knowledge. The curriculum is designed to be interactive, incorporating cognitive behavioral techniques, mindfulness practices, and resilience-building exercises tailored to the realities of youth living in this community. By centering local expertise and youth voices, this intervention seeks to empower participants with the tools needed to manage stress, build emotional resilience, and improve overall mental well-being, while fostering a sense of community support and engagement. The primary aims of this intervention are to (1) increase participants’ knowledge and understanding of anxiety, including its causes, symptoms, and physiological effects; (2) reduce stigma by normalizing conversations around anxiety and seeking different levels of help (eg, peer support, spiritual support, talking to a trusted adult, and therapy); and (3) increase participants’ confidence in managing anxiety by equipping them with practical coping skills to navigate stressors in their daily lives.

## Methods

### Study Setting

The study will be conducted in Paterson, New Jersey, a northeastern urban community with a population of approximately 157,864 residents, with children and youth aged <18 years comprising about 27% of the population [19]. The city faces significant socioeconomic challenges, including a poverty rate of 23.5%, more than double the state average of 9.7%. These economic hardships contribute to increased mental health concerns among residents, particularly youth, highlighting the urgent need for targeted mental health interventions. The study’s principal investigator (PI) has worked with the city as a community-based participatory researcher for almost a decade and leads multiple National Institutes of Health (NIH)–funded studies centered in this community, including a 5-year NIH-funded grant, the Paterson Prevention Project, which examines the impact of neighborhoods on youth substance use and mental health in the city [20]. Using previously published research from work conducted in the target community, and using a community-based participatory approach, the study has identified anxiety as a critical concern among Paterson youth. Addressing anxiety through targeted interventions has emerged as a crucial step in improving mental health access and outcomes in this underserved community.

### Theoretical Framework

The intervention is guided using cognitive behavioral therapy (CBT) principles, a well-established evidence-based approach that targets maladaptive thoughts and behaviors to improve mental health outcomes [21]. In addition to psychoeducation around symptoms of anxiety, CBT also emphasizes skill development and implementation such as breathing techniques, visualization, and graded exposure and role-playing. Given the unique needs of urban youth, adaptations of how CBT will be delivered have been developed to enhance its cultural relevance and effectiveness. Research has demonstrated that culturally tailored CBT interventions for urban youth populations incorporate contextual stressors such as systemic inequities, racial discrimination, and community violence, making the approach more applicable and impactful for these communities [22]. AdditionAdditionally, our intervention integrates principles from trauma-focused CBT, which has been shown to be effective in addressing trauma-related symptoms among youth who have experienced adversity [23]. By incorporating both frameworks alongside trauma-informed strategies, our approach aims to provide a comprehensive and culturally responsive intervention for urban youth facing multiple forms of psychosocial stressors.

#### Theater Testing

Theater testing is a critical step in the development and refinement of an intervention, allowing facilitators to practice the delivery of the curriculum with a small group before full-scale implementation. This process helps identify strengths, areas for improvement, and any logistical or content-related challenges that may arise. By running the intervention in a controlled environment with a representative sample, facilitators can assess whether the activities, discussions, and pacing are engaging and effective for participants. Research supports the use of pilot or feasibility testing in intervention development, as it provides essential feedback to refine content, delivery style, and overall structure, ensuring that the program is both evidence based and practical for real-world application [24]. Additionally, theater testing allows facilitators to become more comfortable with the material, enhancing their ability to deliver sessions with confidence and consistency [25].

In February 2025, the study team conducted a theater test of the intervention with 5 members of our YAB during an 8-hour session in person in Paterson, New Jersey. The facilitators led participants through the full intervention while a designated study team member took notes on participant engagement, clarity of instructions, and areas needing improvement. After completing the session, the study team convened to discuss feedback and make necessary revisions to the curriculum. Additionally, a follow-up meeting was held with the PI to review the final adjustments before moving forward with pilot testing. This iterative process ensures that the intervention is responsive to the needs of the target population, aligns with best practices in youth mental health programming, and is optimized for successful implementation.

### Pilot Study Procedures: Recruitment, Selection, and Consent Process

This study is approved by the institutional review board of Yale University and has been registered on Clinical Trials.gov (NCT07044752). The recruitment plan for the pilot study intervention will involve a collaborative partnership with a local high school, working closely with the principal and lead school counselors to identify youth who may benefit from participation. School counselors and teachers will play a key role in identifying students who exhibit signs of heightened anxiety or have been classified as high risk based on behavioral observations, academic performance, and self-reported concerns. To ensure a targeted and effective approach, recruitment will prioritize students who have been flagged by school guidance counselors for increased anxiety symptoms, difficulty managing stress, or other related mental health challenges. Once identified, eligible students will be invited to participate, with parental consent waived as per institutional review board approval. The intervention cohorts will be divided by sex (self-identified by the youth) to foster a comfortable and supportive group dynamic, allowing for tailored discussions and activities that align with the unique experiences and stressors faced by male and female students. This structured recruitment approach ensures that the intervention reaches those in greatest need while maintaining a supportive and inclusive environment for all participants. After referral to the intervention, the relevant information of the study will be provided to all participants in detail, and they will be given sufficient time to consider whether to participate in the study. If the participants agree to participate in the intervention, they will sign an informed assent form. Parental consent will be waived; however, all parents of youth participants will receive an information sheet indicating that their child is participating in an intervention. No blinding or randomization will occur in this phase of pilot testing. Due to participants being classed as a vulnerable population, they will also be notified of mandated reporter requirements. Each intervention group will consist of 5 to 10 participants, with a preferred group size of 8 with a total sample of 50 participants.

### Intervention Facilitators

The intervention will be facilitated by a license-eligible social worker who is on the study’s YAB and is from the community and a license-eligible clinical psychologist on the study team. Having facilitators from the community is crucial, as research indicates that community-based mentors and professionals foster stronger connections with participants, enhance engagement, and improve intervention outcomes [25,26]. These facilitators bring an intrinsic understanding of local stressors, social dynamics, and cultural nuances that external professionals may not fully grasp. Their presence helps to build trust and relatability, making the youth feel more comfortable discussing their experiences and applying coping strategies. Additionally, incorporating local facilitators into the program fosters sustainability, as they can continue to serve as mental health advocates within their community beyond the duration of the intervention [25,26]. This approach ensures that the program is not only evidence based but also deeply rooted in the strengths and needs of the community it serves.

### Study Measures: Baseline and Posttreatment Tests

The study will be conducted over 5 weeks with multiple assessment points depending on the measure. Outcome measures will be collected at the first session, which will be considered at baseline (T1) and after treatment (T2; 4 weeks from the baseline assessment or after the last intervention session has been completed).

### Primary Outcomes

The primary outcome is the mean change in anxiety scores on the Generalized Anxiety Disorder-7 (GAD-7) questionnaire for adolescents between the baseline, after the intervention, and at the 3-month follow-up (T2). The questionnaire has 7 items, each with a 4-point scale, with scores between 0 and 21 points. Scores are considered as follows: 0 to 4 symptoms (minimal), 5 to 9 symptoms (mild), 10 to 14 symptoms (moderate), and 15 to 21 symptoms (severe). The GAD-7 has demonstrated excellent psychometric properties [27-30]. The items inquire about the degree to which the patient has been bothered by feeling nervous, anxious, or on edge; not being able to stop or control worrying; worrying too much about different things; having trouble relaxing; being so restless that it is hard to sit still; becoming easily annoyed or irritable; and feeling afraid as if something might happen.

### Secondary Outcomes

Secondary outcomes will include the Coping Self-Efficacy Scale, a validated instrument assessing individuals’ confidence in using adaptive coping strategies to manage stressors [31]. Depression symptoms will be assessed using a validated measure such as the Patient Health Questionnaire-9 [32], which will allow us to explore whether reductions in depressive symptoms contribute to improvements in other targeted outcomes. By integrating these measures, we aim to comprehensively evaluate the intervention’s impact and identify key mechanisms driving behavior change.

### Sample Size and Power Justification

This study was powered based on the primary aim of assessing the feasibility of the newly developed intervention. Sample sizes ranging from 24 to 50 have been recommended for feasibility studies [31,32]. With a sample size of 50, we expect to retain at least 80% of the participants at 3 months after the intervention. For primary and secondary aims, we will estimate effect sizes from means and SDs, which will be used to determine the power needed for a future randomized controlled trial.

The planned analyses will include both descriptive and inferential statistics to assess the intervention’s effectiveness. The main outcome of interest will be anxiety. We expect that mean GAD-7 scores in the posttest assessments will be significantly lower than baseline scores. Baseline demographic characteristics, including age, sex, race, and socioeconomic status, will be reported. A repeated measures ANOVA within a within-subjects design will be used to test this hypothesis, with Shapiro-Wilk tests assessing normality assumptions. Based on previous literature that has used these measures, the distribution of difference scores will likely be normal. The study team will also explore whether changes in GAD-7 scores differ by sex. In addition, the study team will conduct statistical analyses to assess the reliability and construct validity of the GAD-7 questionnaire within the sample. Specifically, confirmatory factor analysis and Cronbach α will be used to evaluate the scale’s factor structure and internal consistency. Given previous use of the GAD-7 questionnaire in similar samples of youth of color [27,28], we anticipate that the scale will demonstrate strong psychometric properties in this population [29,30].

Additionally, logistic regression models will estimate the likelihood of clinically significant improvements in mental health and behavioral outcomes based on key predictors, including baseline symptom severity, intervention dosage, and demographic factors. Given the longitudinal nature of our data, we will use linear mixed-effects models to account for within-subject correlations and evaluate changes over multiple follow-up points. These models will help determine whether intervention effects are sustained and whether specific subgroups (eg, sex-based cohorts) exhibit differential responses.

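### The repeated measures ANOVA and the mixed model overlap on GAD-7 change with neither named as primary, and the abstract's one-tailed tests across groups have no stated direction

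*Protocol article*

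**What the plan says.** The analysis text is in the protocol article under Sample Size and Power Justification. The hypothesis is directional: "We expect that mean GAD-7 scores in the posttest assessments will be significantly lower than baseline scores". One test is tied to it: "A repeated measures ANOVA within a within-subjects design will be used to test this hypothesis". Later in the section a second method is added for the longitudinal data: "we will use linear mixed-effects models to account for within-subject correlations and evaluate changes over multiple follow-up points". Its stated purposes are these: "These models will help determine whether intervention effects are sustained and whether specific subgroups (eg, sex-based cohorts) exhibit differential responses". Neither method is called primary, supportive or sensitivity.

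The same section gives the expected follow-up for a sample of 50: "we expect to retain at least 80% of the participants at 3 months after the intervention". It also says that effect sizes estimated from means and SDs will be used to determine the power needed for a future randomized trial.

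The Methods paragraph of the abstract describes the analysis differently: "parametric tests (eg, repeated measures ANOVA and 1-tailed *t* tests) to compare anxiety reduction across groups". The t tests do not appear in the analysis section.

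On timing, the abstract and Primary Outcomes both include baseline, post-intervention and 3 months. Primary Outcomes attaches the label T2 to the 3-month visit. Study Measures: Baseline and Posttreatment Tests defines T2 as post-treatment and lists no 3-month assessment.

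**The concern.** Two methods for repeated GAD-7 scores in the same youth can disagree. With no ranking, the result that counts as the finding could be chosen after both are known.

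The method tied to the hypothesis is also the less suitable of the two for the attrition that the plan expects. A conventional repeated measures ANOVA over three visits needs a score at every visit. A youth who misses only the 3-month visit therefore also drops out of the baseline to post-intervention comparison, although both of those scores exist. If the youth who remain more anxious are the ones lost, that estimate is too favourable, and an effect size taken from it would carry the error into the sizing of the next trial.

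The one-tailed tests raise a separate problem. A one-tailed test needs a direction fixed in advance, and the article gives none for any comparison between groups.

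**Working it through.** **1. Overlap.** The ANOVA tests GAD-7 change over time within person. The mixed model evaluates change over the follow-up points, whether effects are sustained, and subgroup differences. Both therefore estimate the time effect on GAD-7 in the same participants. As an illustration, 20,000 null trials were simulated with N = 50, three visits, correlation 0.6 and 20% missing completely at random at 3 months. A compound-symmetry model with known correlation stood in for the mixed model. Each method rejected in about 5% of trials, and the two gave different verdicts in 3.3%.

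**2. Which visits enter the ANOVA.** The abstract and Primary Outcomes list three time points, and the hypothesis speaks of posttest assessments in the plural. Study Measures lists two. Three visits is the better-supported reading, but the text does not settle it.

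**3. Complete cases under the three-visit reading.** Inputs from the article: N = 50 (minimum 30) and retention of at least 80%.
- 50 × 0.80 = 40, so up to 10 are lost.
- 30 × 0.80 = 24, so up to 6 are lost.

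A mixed model keeps every youth with any GAD-7 score.

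**4. Precision.** Assume SD 5 and correlation 0.6. The SD of a within-person change is 5 × √(2 × (1 − 0.6)) = 4.47.
- Baseline to post-intervention: SE 4.47/√50 = 0.63 with all youth and 4.47/√40 = 0.71 with complete cases. The ratio is √(50/40) = 1.118, so the interval is about 12% wider.
- Baseline to 3 months: SE 0.685 from a likelihood analysis of all 50 and 0.707 from complete cases, a gap of about 3%.

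**5. Bias if more anxious youth drop out.** Same assumptions, with means at both later visits 2.0 below baseline, and 20% lost at 3 months with log-odds linear in the post-intervention score. Complete-case baseline to post-intervention change, against a true -2.0:

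| Dropout odds ratio per SD | Estimated change |
|---|---|
| 1.5 | -2.16 |
| 2 | -2.26 |
| 3 | -2.37 |

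At odds ratio 2, correlations of 0.5 and 0.7 give -2.33 and about -2.2. The baseline to 3-month change stays essentially unbiased under this mechanism.

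**6. Consequence for a later trial.** At odds ratio 2 the overstatement is 2.26/2.0 = 1.13. Required sample size varies as 1/effect². If the next trial were sized on this contrast with SD unchanged, it would come out at 1/1.13² = 0.78 of the correct size, about 22% too small.

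**7. One-tailed tests across groups.** Finalization of Intervention says there are no control conditions, so the groups described are the sex-separated cohorts. The analysis section only says that differences by sex will be explored, and Anticipated Findings says only that there may be differences. No direction is stated. If it is chosen after seeing the data, a nominal 5% test has a true error rate of 2 × 5% = 10%.

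The article gives no alpha, SD, correlation, effect size or dropout mechanism, so there is no power figure to reproduce. Every number beyond the counts in step 3 rests on the assumptions stated.

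**The case against.** A reader might infer that one hypothesis is assigned to three methods and so yields three primary p values. The article does not support that. It ties only the ANOVA to the hypothesis. The mixed model is introduced for sustained effects and subgroups, and the t tests appear only in the abstract, as an example, for comparison across groups. What stands is an overlap between two methods plus a separate, undirected group test.

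A reader might also infer that the plan prescribes dropping youth who miss the 3-month visit. It does not. That follows from the usual form of the method, and only if all three visits enter and nothing is imputed. Under a two-visit ANOVA, F equals t² for exactly the baseline to post-intervention contrast, and loss at 3 months removes nobody from it. Missing-data rules, planned contrasts and sphericity corrections may sit in an analysis plan that is not shown, and their absence is not held against the article.

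A third tempting step is to say that one-tailed testing doubles false claims of improvement. That argument concerns within-person tests of reduction, which do have a stated direction. The abstract assigns the one-tailed tests to groups.

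The size of the problem is also modest. A bias of 0.26 is less than half a standard error (0.63 to 0.71), and it affects one contrast. This is an uncontrolled pilot sized for feasibility. These points limit the weight of the finding. They do not remove the missing ranking, the conflict over T2 or the undirected test.

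**Conclusion.** The point holds in a limited form and should be fixed.

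- From the text alone: two overlapping analyses of the primary outcome are unranked, T2 has two meanings, and the abstract plans one-tailed group tests that have no stated direction and no counterpart in the analysis section.
- On the better-supported three-visit reading, with the conventional method: the ANOVA keeps 40 of 50 or 24 of 30 at the stated retention, while the mixed model that is already planned keeps everyone with a score.
- On assumed values only: the baseline to post-intervention change could be overstated by 0.16 to 0.37 points on a true 2.0 if more anxious youth are lost. This shows direction and rough size and is not a forecast. It matters mainly because the effect sizes are meant to inform a randomized trial.
- If the direction of the group test is picked after seeing the data, its error rate is 10% at a nominal 5%.

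**What to change.** 1. Name the planned linear mixed model as the single primary GAD-7 analysis, with time as a categorical factor and all participants who have any GAD-7 score.
2. Reconcile T2 between Study Measures and Primary Outcomes, and give the 3-month visit its own label.
3. Report both the baseline to post-intervention and the baseline to 3-month contrasts, since Primary Outcomes includes both. State which is primary, and give each an estimate, a two-sided 95% confidence interval and a two-sided p value.
4. Remove the repeated measures ANOVA or label it supportive.
5. Delete the one-tailed group t tests from the abstract or make them two-sided, so that abstract and analysis section agree.

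The cost is wording only, with no new data, visits or participants. Two-sided p values will be somewhat less favourable than one-tailed ones.
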